### Data entry, coding, security, and storage

The contact details of consenting participants will be kept in an Excel spreadsheet that will also contain a unique identifier number. This unique identifier will be generated by computer and will be used to identify participants in the study working database. Data collected via the postal questionnaire and interview with the SCID will be entered manually into an Excel spreadsheet. Data collected via the internet will be recorded automatically and later transported to an Excel spreadsheet, which will then be imported into Stata for statistical analysis (StataCorp, version 13.1). Postal and SCID data will be kept in a locked filing cabinet at the Western Australia Centre for Health & Ageing. Electronic data will be kept in a secure server of the University of Western Australia. Study data will be kept for a minimum of 7 years following completion of the trial.

### Sample size

About 10% of adults with subsyndromal symptoms of depression develop a major depressive episode over the subsequent 12 months
[7]. We anticipate that CBM will be associated with an absolute risk reduction of major depression of 6% over this period (i.e., annual incidence of 4% compared with 0.8% for people free of subsyndromal depression – still high, but lower than controls with subsyndromal depression). This would require that 444 (222 per group) participants provide valid data to ascertain this endpoint of the study (power of 80% and two-tailed alpha of 5%). We further anticipate that as many as 20% of our volunteers may be lost during follow-up, which would require that 532 participants enter the study (266 per group). The number need to treat for one to benefit from CBM would be 17. If the PHQ-9 scores of participants declines, on average, 0.5 points for controls (SD = 4) and 3 points for active CBM participants (SD = 1.5), then a study of this size would have 97% power to declare such difference between the groups as statistically significant (two-sided alpha = 5%). The changes in response bias (measured in ms) are expected to be associated with a minimum effect size of 0.4 (Cohen’s d)
[22], which would require about 50 trials per participant (within group comparison). As each CBM session includes 180 trials for attention (faces) and 180 trials for interpretive bias (words), the study will have ample power to investigate this outcome.

Two of our previous community-based trials showed that 19.8% of mature adults have subsyndromal depressive symptoms
[5,38], indicating that we will need to screen 2,687 community-dwelling people to accrue 532 eligible cases. Response to our previous invitations has been of the order of 15 to 20%. If we assume that 15% of those invited will consent to screening, we will need to invite 18,000 people, to screen 2,687 participants, and recruit 532 into the trial. We will seek to approach 20,000 people.

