**Design and methods:**

This randomised controlled trial will recruit 532 adults with subsyndromal symptoms of depression living in the Australian community (parallel design, 1:1 allocation ratio). Participants will be free of clinically significant symptoms of depression and of psychotic disorders, sensory and cognitive impairment, and risky alcohol use. The CBM intervention will target attentional and interpretive biases associated with depressive symptoms. The sessions will be delivered via the internet over a period of 52 weeks. The primary outcome of interest is the onset of a major depressive episode according the DSM-IV-TR criteria over a 12-month period. Secondary outcomes of interest include change in the severity of depressive symptoms as measured by the Patient Health Questionnaire (PHQ-9), use of antidepressants or benzodiazepines, and changes in attention and interpretive biases. The assessment of outcomes will take place 3, 6, 9, and 12 months after randomisation and will occur via the internet.

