[32,33]. The scale consists of 9 questions about how often the respondent has been bothered by depressive symptoms during the past 2 weeks, and each item can be scored 0 (not at all), 1 (several days), 2 (a week or more) or 3 (nearly every day). The 9 items are: (a) decreased interest or pleasure, (b) low mood, (c) sleep disturbance, (d) lack of energy, (e) disturbed appetite, (f) feelings of failure or guilt, (g) poor concentration, (h) psychomotor disturbance, and (i) suicidal thoughts. The PHQ-9 is a simple self-rating instrument that takes no longer than 5 minutes to complete. Scores between 5 and 14, inclusive, indicate mild or subsyndromal depression.

– Alcohol Use Disorders Identification Test (AUDIT): this 10-item questionnaire has been designed as a screening instrument for risk drinking. The scale takes 2 minutes to complete, and scores ≥15 indicate hazardous/harmful alcohol use or dependency
[34].

Returned screening questionnaires will be immediately scanned and volunteers deemed potentially eligible will be contacted within 2 weeks to organise a telephone interview for the assessment of cognitive function (TICSm)
[35] and, for those free of cognitive impairment, an assessment of current and past mental state with the SCID-I, which is a structured clinical interview for axis I diagnoses that can be administered by trained research staff over the telephone
[36]. It provides reliable and valid information to establish the diagnosis of major depressive episode (recurrent or single episode) according to DSM-IV-TR criteria
[37] (which is consistent with DSM-5 criteria). Participants with a current major depressive episode will be excluded from further participation. Volunteers deemed eligible will be given a user name and password to access the CBM website. When they first login, their username will be linked to a number from a random list of study numbers, which will be randomly assigned to either the intervention or control CBM. Additional lists will be requested from the Australian Electoral Commission until the total number of participants enrolled in the study reaches the required number of 532 people.

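### The 20% loss allowance multiplies 444 by 1.2 instead of dividing by 0.8, so enrolling 532 leaves about 426 evaluable, not 444

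*Protocol article*

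**What the plan says.** The Sample size section of the protocol article links three figures.

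- Evaluable number: "This would require that 444 (222 per group) participants provide valid data to ascertain this endpoint of the study". It is tied to 80% power, a two-tailed alpha of 5%, and 12-month incidences of 10% (control) and 4% (active).
- Loss and enrolment: "as many as 20% of our volunteers may be lost during follow-up, which would require that 532 participants enter the study (266 per group").

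Enrolment of 532 is the operative target. The Abstract says "This randomised controlled trial will recruit 532 adults", and Participants and setting opens with the same number. That section also provides for further electoral lists until enrolment "reaches the required number of 532 people". The screening and invitation numbers at the end of Sample size (2,687 and 18,000) are built on 532. No other part of the article gives a different loss rate or another rule for the allowance.

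**The concern.** The loss is expressed as a proportion of volunteers, that is, of people who enter the trial. If 20% of entrants are lost, 80% remain, and the evaluable number must be divided by 0.8. The stated 532 is too small for that, and it is what one gets by adding 20% of the evaluable number to itself.

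At stake is whether the enrolment target delivers the number of primary-endpoint assessments that the plan says it needs, under the plan's own assumption. Recruitment stops at 532, so the shortfall is built into the design and does not depend on recruitment going badly.

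**Working it through.** **Inputs, all from Sample size unless noted.** Evaluable number 444 (222 per group); loss 20% of volunteers; enrolment 532 (266 per group); incidence 10% versus 4%; two-sided alpha 5%; 1:1 allocation (Trial design).

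**1. Reproduce the plan's figure.**
- n × (1 + d): 444 × 1.2 = 532.8 in total and 222 × 1.2 = 266.4 per group. Rounded down, these are exactly the stated 532 and 266.
- The implied loss is 532 − 444 = 88 people. That is about 20% of 444 (88.8), whereas 20% of 532 would be 106.4.

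**2. Apply the loss to entrants.**
- n / (1 − d): 444 / 0.8 = 555. With equal arms, 222 / 0.8 = 277.5, so 278 per group and 556 in total.
- Gap to the stated target: 555 − 532 = 23, or 24 with equal arms. Rounding explains less than one participant of this.

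**3. What 532 delivers.**
- 532 × 0.8 = 425.6, about 426 evaluable (212.8, about 213, per group).
- Shortfall: 444 − 426 = 18, and 18/444 = 4%.
- Largest loss that still leaves 444: 1 − 444/532 = 16.5%.

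**4. Effect on power.** Normal approximation with pooled variance under the null:

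Power = Φ{ [0.06 − z √(2 × 0.07 × 0.93 / n)] / √[(0.10 × 0.90 + 0.04 × 0.96) / n] }, with n per group.

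| n per group | Two-sided 5% (z = 1.960) | One-sided 5% (z = 1.645) |
|---|---|---|
| 222 | 69.9% | 79.9% |
| 213 | 68.1% | 78.4% |
| Drop | 1.8 points | 1.5 points |

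The one-sided column is shown because a one-sided 5% test at 80% power needs 223 per group by this method, close to the stated 222. The two-sided test named in the plan needs 283 per group (566 evaluable). That discrepancy is a separate matter. It is why the two-sided column starts at 69.9% and not 80%.

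**The case against.** The arithmetic is not in dispute. The case on the other side is that it matters little and should not be inflated.

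- **The 20% is worded as a ceiling.** At any loss up to 16.5%, 532 still yields 444, so the full shortfall of 18 appears only at the ceiling. This is true, but the sentence presents 532 as the enrolment that this ceiling requires, and at the ceiling it falls short.
- **The panel analysis softens the loss.** Statistical methods plans an intention-to-treat repeated-measures analysis, and someone lost after month 3, 6 or 9 has already contributed SCID-I data. The real loss of information may therefore be smaller than the power figures suggest. This stands as a caution on the size of the effect. It does not reconcile the figures, because Sample size asks for 444 with valid endpoint data and takes no quantified credit for partial follow-up.
- **Most of the distance from 80% power belongs elsewhere.** Of the roughly 12 points between 80% and 68.1%, about 10 come from the 444 itself. This stands: the part due to the loss allowance is 1.5 to 1.8 points.
- **555 is odd under 1:1 allocation.** Also correct. The equal-arm figure is 556.

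**Conclusion.** The concern holds. The three figures in Sample size cannot all be true: 444 evaluable, 20% of entrants lost, 532 entered. The error is an allowance calculated on the wrong base, and it leaves enrolment 23 short (24 with equal arms).

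Taken alone the effect is modest. Even on the one-sided basis that comes closest to the plan's 222 per group, power under the plan's own loss assumption is 78.4%, below the stated 80%. The power figures rest on 10% versus 4%, a simple comparison of two proportions, and lost participants contributing nothing. The shortfall in numbers rests only on the plan's own 444, 20% and 532.

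**What to change.** Correct the sentence in Sample size in one of three ways.

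1. **Keep 532 and state what it gives:** with 20% loss, about 426 evaluable (213 per group) and 68% two-sided power for 10% versus 4%.
2. **Keep 532 and 444 and restate the loss:** 532 absorbs the loss of 88 participants, or 16.5%.
3. **Keep 444 and 20% and restate enrolment:** 555, or 556 (278 per group) with equal arms. Change 532 in the Abstract, in both places in Participants and setting, and in the screening figures.

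Options 1 and 2 are text corrections only. Option 3 adds 24 participants. At the plan's 19.8% eligibility and 15% response, 556/0.198 is about 2,809 screened (against 2,687), and dividing by 0.15 gives about 18,700 invited, within the 20,000 already planned.

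Make the correction together with a review of the 444. Neither option 2 nor option 3 gives the stated two-sided 80% power, because 444 does not provide it. If the evaluable number were revised to the 566 that the stated two-sided test needs, the loss step would have to be redone by division: 566/0.8 = 707.5, so 708.

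### The 97% power stated for PHQ-9 change does not follow from the means, SDs and sample size printed with it, which give power above 99.99%

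*Protocol article*

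**What the plan says.** The Sample size section of the protocol article sizes the trial on the onset of a major depressive episode. It asks that "444 (222 per group) participants provide valid data to ascertain this endpoint of the study", allows that "as many as 20% of our volunteers may be lost during follow-up", and concludes that this "would require that 532 participants enter the study (266 per group").

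It then adds a power statement for the change in PHQ-9 score. The assumed average declines are "0.5 points for controls (SD = 4) and 3 points for active CBM participants (SD = 1.5"). On that basis, "then a study of this size would have 97% power to declare such difference between the groups as statistically significant", with a two-sided alpha of 5%. The Trial design section fixes 1:1 allocation.

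The Outcomes and study measures section lists change in PHQ-9 severity as a secondary outcome. The Statistical methods section plans a multilevel mixed model for it and says that the repeated-measures approach raises power.

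**The concern.** Everything needed to check the 97% is printed beside it: two means, two SDs, alpha, sidedness and group size. A difference of 2.5 points against SDs of 4 and 1.5, with more than 200 participants per group, should leave almost no chance of a non-significant result. A power of 97% is what a much smaller study, or a much smaller difference, would give.

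If the power figure is the slip, the sentence merely understates power under its own assumptions. If a mean or an SD is the slip, the published planning effect is not the one that was used. Anyone who later sets the PHQ-9 result against the protocol would then be using the wrong benchmark.

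**Working it through.** **Inputs** (protocol article, Sample size, except the allocation ratio, which is in Trial design)
- Control: mean decline 0.5, SD 4.
- Active CBM: mean decline 3, SD 1.5.
- Difference: 3 − 0.5 = 2.5 points.
- Two-sided alpha 5%, so the critical value is 1.960.
- Allocation 1:1. Group size is 222 (evaluable, as stated), 266 (enrolled), or 266 × 0.8 = 212.8, about 213 (enrolled less the stated 20% loss). All three are tried because the text says only that the study is of this size.

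**Formulas**
- SE = √(4²/n + 1.5²/n) = √(18.25/n).
- Power ≈ Φ(2.5/SE − 1.960), checked with the noncentral t for unequal variances (Welch).

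**Attempt to reproduce 97%**

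| n per group | SE | 2.5/SE | Power |
|---|---|---|---|
| 213 | 0.293 | 8.54 | above 99.99% |
| 222 | 0.287 | 8.72 | above 99.99% |
| 266 | 0.262 | 9.54 | above 99.99% |

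The Welch calculation agrees in every row. Power of 97% corresponds to a ratio of 1.960 + 1.881 = 3.841, less than half of any ratio in the table. The figure is not reproduced.

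**What would give 97%**
- *Group size*, keeping the printed means and SDs: n = 18.25 × 3.841²/2.5² = 43.1, so 44 per group by the normal approximation. With the Welch t, 45 per group gives 97.1%.
- *Difference*, keeping the printed SDs: 3.841 × √(18.25/n) = 1.12 points at 213, 1.10 at 222 and 1.01 at 266.
- *Common SD*, keeping the 2.5-point difference: 2.5/(3.841 × √(2/n)) = 6.7 at 213, 6.9 at 222 and 7.5 at 266. All are well above either printed SD.

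**Other readings tried**

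| Reading | n per group | Power |
|---|---|---|
| SD 4 in both arms | 213, 222, 266 | above 99.999% |
| Alpha 1% instead of 5% | 222 | above 99.9999% |
| Rank test, efficiency 0.864 | 222 | above 99.9999% |
| Groups half the size, printed SDs | 111, 133 | above 99.99% when rounded (99.998% or more) |
| The two SDs added to a common SD of 5.5 | 213, 222, 266 | 99.7%, 99.8%, 99.9% |

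None of these comes within 2 percentage points of 97%. The summed SD of 5.5 does give 96.0% at 133 per group, but that is half the trial and needs a second departure from the text.

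**Changed inputs that come close** (illustration only)
- A 1.0-point difference with SDs 4 and 1.5 at 266 per group: 96.8%.
- A 1.5-point difference with SD 4 in both arms: 97.2% at 213 and 97.7% at 222 per group.

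So a misprinted mean or SD is possible, but nothing in the document picks out one of these.

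**The case against.** The best reply is that the discrepancy is harmless. The major-depressive-episode endpoint sets the trial size, and PHQ-9 change is secondary. For the printed inputs the stated power is too low rather than too high, and correcting it alters no visit, analysis or decision rule. All of that stands, and it limits the importance of the point. It does not make the sentence right: the printed inputs and the printed result cannot both hold.

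Several stronger readings are tempting, and the document does not support them.

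- A reader might infer that the power is the wrong figure and that the trial can therefore detect differences of about 1 point. That takes the printed SDs as correct, which is exactly what the inconsistency leaves open.
- A reader might infer that the sentence makes the trial look barely adequate for PHQ-9. It does not: 97% is far above the 80% used for the primary endpoint, and either figure signals ample power for 2.5 points.
- A reader might infer that the active-arm SD of 1.5 is itself a mistake, being less than half the control SD and given without a reason. Unequal SDs are unusual but not contradictory, and a condensed article may leave the reason to the full protocol.
- A reader might want to substitute SD 4 in both arms and quote a detectable difference. That would replace a printed assumption with one the protocol does not make.

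**Conclusion.** The inconsistency is real and can be checked from a single sentence. With the printed means, SDs and alpha, power is above 99.99% at 213, 222 or 266 per group, not 97%. At least one of the power, the means and the SDs is wrong as printed, and the document does not say which.

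The check rests on a plain two-group comparison of mean change with the printed SDs taken as SDs of change. The section names no multiplicity adjustment or design effect that would lower power. By the protocol's own account the planned repeated-measures model adds power, so it would not pull the figure down towards 97%.

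The consequence is confined to a secondary outcome. Enrolment and the primary analysis stand as they are with respect to this point. What is uncertain is either the stated power or the effect the investigators planned for.

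**What to change.** Go back to the original PHQ-9 power calculation and correct the sentence in one of two ways.

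1. If the printed means and SDs are the ones used, restate the power as above 99.9% for a 2.5-point difference.
2. If a mean or an SD was misprinted, print the intended value and confirm that the stated power follows from it at the evaluable sample size, naming that size in place of the present general reference to the study's size.

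The cost is one look at the original calculation and one revised sentence. No change to sample size, assessments or analysis follows.

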### Randomisation and blinding

Participants will be assigned to one of the two treatment arms of the study according to lists of random numbers generated by computer in random permuted blocks of 8 to 20. The lists will be generated and maintained by the Centre for Software Practice of the University of Western Australia, which will have no direct contact with participants. Neither staff nor participants will be aware of group assignment. Participants will be instructed that the focus of their activity is to identify the orientation of the probe (vertical or horizontal) and the missing letter of the word fragment as quickly as possible. In this respect, control and active CBM tasks are indistinguishable. Research staff involved in the collection of endpoints will be directed not to discuss with participants any aspects of the intervention. Unblinding will only occur once the final endpoint of interest is collected from the last participant in the trial.

All logins and logouts will be recorded automatically, so that the trial will have an objective measure of the adherence of participants to the scheduled activities. In order to optimise the completion of scheduled activities of the study, participants will receive an automated text message and/or email (as per stated preference) alerting them to upcoming study activities for the week ahead and encouraging them to complete the relevant tasks. Once an activity is completed, participants will receive a text/email thanking them and outlining the next activity in their schedule.

### Statistical methods

We will use means and standard deviations to describe continuous variables with normal distribution, medians, and inter-quartile ranges for ranked variables, and frequency tables for categorical variables. We will evaluate the primary endpoint of the study by considering the proportion of participants showing evidence of depression during follow-up. Our approach to the analysis will be intention-to-treat and will use panel data accrued at different time points. We will use the command ‘xtlogit’ of the statistical package Stata 13.1 to complete these analyses, and models will be adjusted for imbalances that might be present at baseline. This approach to the analysis will also allow us to investigate interactions between treatment group and time. Similarly, we will use multilevel mixed models to analyse changes in PHQ-9 scores and in attentional and interpretive biases from baseline to month 12. We will investigate the interaction between group and time effects (statistical adjustments will be made, if necessary). This analysis will also be intention-to-treat. This approach to the analysis of the data (panel; repeated measures) increases study power and lessens the impact of missing data. All probability tests will be two-tailed (*P* <0.05).

## Discussion

Depression is a leading cause of disability and health expenditure in Australia and worldwide. Attempts to develop strategies to prevent depression have focused predominantly on people at high risk, such as those with subsyndromal symptoms, although results have been mixed and costs high. COPE will test the efficacy of a highly innovative intervention that is well grounded in theory and for which increasing empirical evidence for an effect on mood is available. We used best available evidence to estimate the number of people with subsyndromal symptoms of depression likely to develop a depressive episode over a 1-year period
[7], and a schedule of activities designed to shift existing biases during the first few weeks of treatment and progressively less frequent booster sessions designed to sustain these changes. The intervention targets both attentional and interpretative biases, as this seems to enhance treatment response
[30]. This intervention is simple, inexpensive, easy to access via the internet, and could be easily rolled out into practice if our findings confirm a role for CBM in the prevention of depression. Our strategy to recruit participants has been used successfully before and will give us the flexibility to expand recruitment in a timely manner, if necessary. All study procedures have been piloted: they are working as planned and have been well accepted by users. We anticipate that we will need three years to complete the collection of all outcomes of this study.

